## Secondary endpoints

Important secondary endpoints are:

- Body weight
- Length
- Head circumference

These will be modelled by a linear mixed effects model. Subject will be used as a random factor, and *GA* and *treatment* will be used as fixed factors. The hypothesis of interest is if there is a significant difference in the slope, i.e. that the growth rate is different in the two groups.

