| Number of Subjects:        | 45 subjects receiving Omega-3 supplementation and 45 subjects receiving conventional fatty acid supplementation.                                                                                                                                                                                                                                                                                                                                                                |
| Subject Population:        | 90 premature male/female infants, born before gestational age 28 weeks+ 0 days.                                                                                                                                                                                                                                                                                                                                                                                                 |
| Dosage:                    | All infants on parenteral nutrition from birth and as long as clinically indicated are given fatty acid supplementation (Clinoleic). In addition, children randomized to Omega 3 supplementation receive SMOFlipid® with a quotient between Omega-6 and Omega 3 that is 2.5:1.                                                                                                                                                                                                  |
| Study Duration:            | From birth to 40 postmenstrual weeks                                                                                                                                                                                                                                                                                                                                                                                                                                            |

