| Primary Study Objectives:  | 
A) The objective of this study is to determine how fatty acid (FA) levels in prematurely born children are affected by supplementation of “physiologic levels of long chain polyunsaturated fatty acids (LCPUFA) i.e. Omega-3 and 6
 
B) To determine whether these FA levels protect against development of retinopathy of prematurity (ROP)
                                                                                                                       |
| Secondary Study Objective: | 
C) To determine whether these FA levels normalize growth (length, weight, head circumference) and/or
 
D) To determine whether these FA levels reduce the risk of lung, brain and gut morbidity
                                                                                                                                                                                                                                                                     |
| Efficacy Endpoints:        | 
To compare in supplemented versus conventionally treated children
 
A) Serum and breast milk FA levels at days 1, 7, 14, 28 and in postmenstrual weeks 32, 36 and 40 and from breast milk FA levels day 7 and postmenstrual weeks 36 and 40.
 
B) Development of ROP
 
C) SDS score with regard to length, weight and head circumference growth.
 
D) Bronchopulmonary dysplasia, brain development on MRI examination and necrotizing enterocolitis
 |

**Safety Endpoints:** Adverse events, clinical chemistry, retinal exam, physical examination, vital signs.

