### 4 STUDY DESIGN

The study is a Randomised Intervention, Single-Center Study to Determine the Role of Fatty Acids in Serum and Breast Milk in preventing Retinopathy of Prematurity

Subjects who meet all inclusion and none of the exclusion criteria will be enrolled into the study. Upon entry into the study, subjects will be randomized and given a unique subject number.

A randomised intervention study of 45+45 (number based on power analysis regarding up to date ROP frequency, see 5.1 and 11.1) infants without major malformations born with a gestational age less than 28 weeks + 0 days will be performed.

Randomization of the patients to either

- 1) Conventional fatty acid supplementation regime with Clinoleic (with Vitalipid infant and Soluvit supplementation) to the preterm infant

Or

- 2) SMOFlipid® (with Vitalipid infant and Soluvit supplementation), where the quotient of Omega 6:3 is 2.5:1 in order to mimic the physiologic relation of FAs in cord blood from birth, to the preterm infant.

Thus there is one group of infants (n=45) that will receive Omega-3 in the fatty acid supplementation. The time on parenteral nutrition and the amount of fatty acids given will be according to clinical routines. The randomization of the patients will be performed by the controller of the study Randomization will be in blocks with 10 children in each block.

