**Growth**

Length, weight and head circumference will be registered weekly from birth until 40 weeks postmenstrual age and at 2.5 and 6 years.

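### The growth model as listed has no treatment-by-time term, so it does not contain the slope difference named as its hypothesis, and adding that term with a random intercept alone would make the test too liberal if growth rates differ between infants

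*Protocol*

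**What the plan says.** Protocol section 11.1, under Secondary endpoints, calls body weight, length and head circumference important and assigns them a linear mixed effects model. The random part is one clause: "Subject will be used as a random factor". Of GA and treatment it says that they "will be used as fixed factors". No interaction and no random slope is listed. The next sentence gives the question: "The hypothesis of interest is if there is a significant difference in the slope", which it explains as unequal growth rates between the arms.

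Three other places bear on this:

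- **Meaning of GA.** The abbreviation list expands GA as gestational age and says no more. Section 4 uses gestational age for age at birth (infants "born with a gestational age less than 28 weeks + 0 days"), as does section 3. Section 2 uses it for a span running to 40 weeks, and sections 4 and 8.2 and Table 1 use gestational weeks for sampling times after birth.
- **Schedule.** Section 8.1, Growth: "Length, weight and head circumference will be registered weekly from birth until 40 weeks postmenstrual age and at 2.5 and 6 years".
- **Outcome scale.** The efficacy endpoints in the synopsis name the "SDS score with regard to length, weight and head circumference growth". Section 11.1 names the three body measurements and does not mention SDS.

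**The concern.** The list of model terms and the hypothesis stand in consecutive sentences and do not match. A treatment main effect is a difference in mean level. A difference in growth rate is a treatment-by-time effect. An analyst who fits the listed terms answers the level question. One who tests the slope has to add a term that the protocol does not list.

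The obvious repair carries its own risk. If only the interaction is added and subject stays a random intercept, true differences in growth rate between infants are left out of the standard error of the slope contrast. With a dozen or more weekly values per infant, the model then treats much of that between-infant variation as if it averaged out over measurements. It averages out only over infants. The growth result would rest on confidence intervals that are too narrow.

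**Working it through.** **Is there a figure of the plan's own to reproduce?** Not for growth: section 11.1 gives no power, sample size or error rate for it. Its one figure, 40 per group for 80% power, belongs to the Mann-Whitney test of ROP. Simulation from the tabulated ROP distributions gives about 78% power with and 80% without continuity correction, so that figure stands.

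**Step 1: what the listed terms can estimate.** Write infant i at time j.

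- GA as running age: y_ij = b0 + b1·GA_ij + b2·treat_i + u_i + e_ij. The slope is b1 in both arms, and b2 is a vertical shift.
- GA as age at birth: y_ij = b0 + b1·GA_i + b2·treat_i + u_i + e_ij. Nothing varies with time, so there is no growth slope.

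Neither version has a parameter for a between-group difference in slope.

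**Step 2: interaction added, random intercept kept.** Inputs:

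- n = 45 per arm (synopsis: "45 subjects receiving Omega-3 supplementation and 45 subjects receiving conventional fatty acid supplementation").
- T weekly values per infant. From just under 28 weeks to 40 weeks is 12 weeks, so 13 values including birth; an infant born a week earlier has 14. The later visits are left out.
- Residual variance s² and between-infant slope variance v. The protocol gives neither. Let Sxx be the sum of squared deviations of the measurement times, and k = v·Sxx/s². The range of k is an assumption.

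For balanced data under the null hypothesis:

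- True variance of one infant's fitted slope: v + s²/Sxx = (s²/Sxx)(1 + k).
- Variance that the intercept-only model reports: its residual mean square absorbs v·Sxx spread over T − 1 degrees of freedom, giving (s²/Sxx)(1 + k/(T − 1)).
- Ratio of true to reported variance: R = (1 + k)/(1 + k/(T − 1)).
- Type I error at nominal two-sided 5%: 2·[1 − Φ(1.96/√R)].

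Example, T = 14, k = 1: R = 2/(1 + 1/13) = 1.86, √R = 1.36, 1.96/1.36 = 1.44, type I error 15.0%.

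| k | R, T = 13 | Type I error, T = 13 | R, T = 14 | Type I error, T = 14 |
|---|---|---|---|---|
| 0 | 1.00 | 5.0% | 1.00 | 5.0% |
| 0.5 | 1.44 | 10.2% | 1.44 | 10.3% |
| 1 | 1.85 | 14.9% | 1.86 | 15.0% |
| 2 | 2.57 | 22.2% | 2.60 | 22.4% |
| 4 | 3.75 | 31% | 3.82 | 31.6% |

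**Step 3: simulation.** With 4,000 runs per setting, 45 per arm and T = 13, the intercept-only interaction test rejected in 5.4%, 10.9%, 14.5% and 22.4% of runs at k = 0, 0.5, 1 and 2, and in 41.5% at k = 10. With T = 14 it rejected in 10.9%, 15.0%, 22.6% and 31.7% at k = 0.5, 1, 2 and 4. A test on per-infant slopes, which is what a random-slope model amounts to in balanced data, stayed between 4.3% and 5.4% throughout.

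**Step 4: what k means.** For T = 14, Sxx = 14·(14² − 1)/12 = 227.5. Then k = 1 needs a between-infant slope SD of √(1/227.5) = 0.066 residual SDs per week, and k = 4 needs √(4/227.5) = 0.13.

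**The case against.** The best defence is that the tested contrast is named in words. Speaking of a slope makes most sense with GA as the time axis, and a competent analyst would then fit the GA-by-treatment term. Random-effects structure is also commonly settled in a statistical analysis plan, which is not at hand. Much of this stands: an interaction was probably intended, and silence about a random slope would not be a fault by itself. It does not remove the point, because the protocol chose to list the terms as well as the hypothesis, and the two disagree.

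Four stronger readings are tempting and not supported:

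- That the protocol specifies a random intercept only. It says subject is a random factor; the intercept is the usual reading, not a stated restriction.
- That GA is defined as age at birth, so that the model certainly has no time axis. The abbreviation list does not say so, and the protocol uses the term both ways.
- That the growth test will have a false-positive rate of 10% to 32%. This needs an intercept-only fit and the assumed k, and at k = 0 there is no inflation.
- That the trial's main conclusion is at risk. The ROP comparison does not use this model.

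**Conclusion.** The mismatch between listed terms and hypothesis is certain from the text and needs no assumption. The error inflation is conditional. It arises if treatment x time is added, subject is fitted as an intercept only, and infants differ in growth rate. Under those conditions, with weekly data to 40 weeks and 45 per arm, type I error runs from about 10% at k = 0.5 to about 32% at k = 4. The arithmetic assumes a linear trend and balanced data. Modest variation is enough to reach that range, but the protocol gives no variance components, so where this trial would fall is unknown.

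The outcome scale is a separate inconsistency. A slope in SDS is drift relative to a reference, and a slope in the measurement itself is growth per week. They are different quantities, and the synopsis and section 11.1 do not name the same one.

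The endpoints are secondary, though called important, and the remedy is wording. This should be corrected before outcome data by arm are seen, but it is not a defect that must hold up the trial.

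**What to change.** In section 11.1, Secondary endpoints:

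1. Define time as postmenstrual age, and enter gestational age at birth as a separate covariate.
2. List treatment x time as a fixed effect and name it as the tested parameter, reported with its 95% CI.
3. Specify a random intercept and a random slope for time for each infant.
4. Fix in advance the form of the time trend, the measurements that enter the model, and the single slope contrast to be tested. If the trend is not taken as linear, say beforehand which contrast represents the slope, so that it is not chosen from the data.
5. State whether the outcome is an SDS or the measurement itself, and align the synopsis with section 11.1. The choice is the sponsor's, since it changes the quantity estimated.

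No new data are needed. The price is wider intervals than an intercept-only fit would report: by √R, about 1.20, 1.36, 1.61 and 1.96 times at k = 0.5, 1, 2 and 4 with 14 values. That width reflects uncertainty that the narrower intervals would leave out.

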## 11.2 Study Populations

All available subjects will be used in the data summaries and the listings of subject data. If a subject is regarded as non-evaluable this subject may be listed separately and not included in the summary statistics.

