## **5 STUDY SUBJECTS**

### **5.1 Number of Subjects**

For efficacy evaluations, 80 subjects need to be included for statistical considerations. However, to compensate for protocol violations and withdrawals up to 90 subjects will be included (see **11.1 De-termination of Sample Size and Statistical Methods** on page 26).

After the first 20 subjects have been treated and evaluated there will be a safety check to confirm that the safety profile is acceptable and that the assumption of a 50% reduction in ROP incidence is reasonable. A second safety check will be performed after the next 20 subjects.

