### **6.3 Blinding**

This is a randomised study with blinded ophthalmologic assessment of ROP stage. Retinal examination will be performed approximately once weekly starting at four to five weeks of age according to a standardized protocol and to clinical screening praxis. The assessing, evaluation of ROP stage 3 or more, independent from the study, pediatric ophthalmologists will be unaware which infants are participating in the study.

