#### ROP examination

The retinal examination will be performed once weekly starting at five to six weeks of age according to a standardized protocol and to clinical screening praxis. The ophthalmologic assessment will be performed with strict criteria according to general Swedish Guidelines issued by the Swedish Ophthalmological Society: The Guidelines are available at following link: [www.swedeye.org/SOTA/rop/SOTA-ROP\\_2006.pdf](http://www.swedeye.org/SOTA/rop/SOTA-ROP_2006.pdf).

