## **10 STUDY MANAGEMENT**

### **10.1 Subject Discontinuation**

A discontinuation occurs when an enrolled subject ceases participation in the study, regardless of the circumstances, prior to completion of the protocol.

The investigator has the right to remove a subject at any time if it is in the best medical interest of the subject.

Subjects will be discontinued from treatment prior to completion for any of the following reasons:

- Consent withdrawn / the parents/guardians wish to discontinue study treatment
- AE (clinical events or laboratory values) that contraindicate continuing the study.
- Best interest of the patient, as judged by the Investigator
- Protocol violation

- Administrative Decision
- Other, by Investigator specified reason

Subjects withdrawn from the study for a SAE should be followed until the SAE has resolved. Appropriate supportive and/or definitive therapy should be administered as required.

The investigator must determine the primary reason for discontinuation. The reason for a subject discontinuing from the study will be recorded on the case report form. Withdrawal due to an adverse event should be distinguished from withdrawal due to other reasons, according to the definition of an adverse event noted earlier. A discontinuation must be reported immediately to the Kabi Fresenius AB safety monitor or his/her designated representative if it is due to an adverse event. The **End of Study** examination / sampling must be performed at the time of the study discontinuation. The investigator will record the reason for study discontinuation, provide or arrange for the appropriate follow-up (if required) for such subject, and document the course of the subject's condition.

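### The protocol's only analysis-population rule lets randomised infants be set aside as non-evaluable, undefined and with no stated blinding, so the primary comparison can lose infants after allocation is known

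*Protocol*

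**What the plan says.** - **Population (Protocol 11.2).** The default is inclusive: "All available subjects will be used in the data summaries and the listings of subject data". The exception follows at once: "If a subject is regarded as non-evaluable this subject may be listed separately and not included in the summary statistics". The section gives no criterion, decision-maker, timing or blinding.
- **Numbers (Protocol 5.1).** "For efficacy evaluations, 80 subjects need to be included for statistical considerations". Then, "to compensate for protocol violations and withdrawals up to 90 subjects will be included".
- **Primary test (Protocol 11.1).** A Mann-Whitney test on ROP graded 0, 1, 2, 3, 3+, with a two-sided alternative. The section names no analysis set.
- **Blinding (Protocol 6.3).** "This is a randomised study with blinded ophthalmologic assessment of ROP stage". Section 11.4 repeats this for the ophthalmologist who evaluates stage 3 or more. No blinding is described for anyone else.
- **Discontinuation (Protocol 10.1).** Discontinuation is defined as ceasing participation. The reasons listed for discontinuing treatment include protocol violation, the investigator's view of the patient's best interest, and any other reason the investigator specifies. The end-of-study examination "must be performed at the time of the study discontinuation".
- **Timing of ROP examinations (Protocol 8.1).** Retinal examination takes place "once weekly starting at five to six weeks of age". Section 6.3 gives four to five weeks instead; the two need to be reconciled.

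**The concern.** Randomisation protects the primary comparison only if the decision about who is counted is independent of the arm, or if everyone is counted. Here an infant can be declared non-evaluable on unstated grounds, by an unnamed person, with no requirement that this person be blind. The sizing argument in 5.1 points the same way: a surplus for violators and withdrawals is needed only if they are expected not to contribute to the 80.

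Section 10.1 adds a route by which outcomes can be lost. An infant discontinued in the first weeks has the final study examination before ROP screening begins under either stated start. Routine screening would normally yield a grade later, but the protocol does not say that it will be used.

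If sicker infants are set aside more readily in one arm, that arm's ROP distribution improves without any treatment effect. Blinded grading keeps each stage honest but cannot correct the choice of which stages enter the test.

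**Working it through.** **Inputs from the protocol.** Control distribution 26/15/24/18/17% and active distribution 49/19/19/9/4% for stages 0/1/2/3/3+ (11.1); two-sided 5% level, 80% power, 40 per group (11.1); 45 + 45 randomised (section 4), which is nine blocks since "Randomization will be in blocks with 10 children in each block"; allowance 90 − 80 = 10 infants (5.1).

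**Step 1: reproduce the plan's own figures.**
- The assumed benefit (25% unchanged, 25% down one step, 50% down two), applied to the control row, gives for stage 0: 0.26 + 0.75 × 0.15 + 0.50 × 0.24 = 0.4925. The full row is 49.3/18.8/19.0/8.8/4.3%, which matches the active row.
- P(control worse than active, ties counted half) = 0.26 × 0.245 + 0.15 × 0.585 + 0.24 × 0.775 + 0.18 × 0.915 + 0.17 × 0.98 = 0.669.
- Noether: N = (1.960 + 0.842)² / [12 × 0.25 × (0.669 − 0.5)²] ≈ 92. Multiplying by the tie factor 1 − Σp̄³ = 0.929 gives about 86. Whitehead's proportional-odds formula gives 65. These bracket 80.
- Simulation of the tie-corrected test, Z = (U − n₁n₂/2)/√V with V = (n₁n₂/12) × [(N + 1) − Σ(t³ − t)/(N(N − 1))], rejecting if |Z| > 1.96, gives power of 79.0% at 40 per arm. The stated sample size stands.

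**Step 2: what selective exclusion could do (assumed scenario).** Both arms follow the control row, so there is no true effect; 45 are randomised per arm. Drop k per arm: at random in control, only from stage 3 or 3+ in active. The mechanism is visible by hand. The expected number at stage 3 or worse is 45 × 0.35 = 15.75. After removing 5 from the active arm the share is 10.75/40 = 26.9%, while control stays at 35% on average.

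| k per arm | Two-sided type I error |
|---|---|
| 0 | 5.0% |
| 1 | 5.3% |
| 2 | 6.0% |
| 3 | 7.1% to 7.3% |
| 5 | 11.0% to 11.2% |

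The ranges are across separate simulation runs. At k = 5 about 10.3% to 10.5% falls in favour of active, where 2.5% is nominal. Five per arm is exactly the allowance of 10.

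**Step 3: range around that assumption.**
- Exclusion at random in both arms, k = 1 to 5: 4.9% to 5.1%, so no inflation.
- Harsher case, removing the k worst-graded infants from active and none from control: 5.6%, 6.7%, 8.7%, 11.4% and 14.9% for k = 1 to 5.

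**Step 4: power if everyone is kept.** With 45 per arm and the plan's two rows, power is 83.6%, against 79.0% with 40 per arm.

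**The case against.** The case on the other side has weight, and it limits what can be claimed.

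- **The exception is permissive and names only summary statistics.** True. A reader might infer that the primary result does exclude randomised infants. The text does not say so: 11.1 excludes nobody, and extending 11.2 to the Mann-Whitney test is an inference from 5.1 and 11.2 read together. What stands is that exclusion is possible.
- **Over-enrolment is ordinary planning.** Also true. A reader might infer that violators are replaced. Section 5.1 only compensates in the total, and a surplus could serve for missing outcomes or dilution. But protocol violations are named as a reason, and a violator with a grade needs no compensation for loss if analysed as randomised.
- **The trial is not called open-label, and ROP assessment is blinded.** Correct, and the blinding is a real safeguard for the grade. That the person judging evaluability knows the arm is inferred from silence. The safeguard still does not cover that judgement.
- **Later routine grades are not said to be discarded.** Correct. Section 10.1 also asks for follow-up where required and for documentation of the infant's course. The protocol leaves their use open.
- **Handling of deaths belongs in an SAP.** Accepted. The 0 to 3+ scale has no place for an infant who dies before screening, but how to rank death is a design choice for the SAP and is not charged as an error here.
- **The simulated pattern is invented.** No section suggests such asymmetry. Infants lost before screening have no stage to be selected on, so any link would run through general illness and be weaker. The 11% shows what the rule permits and is not a forecast.

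**Conclusion.** The point holds as a badly fixed rule. The sole population rule allows discretionary removal of randomised infants on undefined grounds, the sample-size text implies that violators and withdrawals need not count, and no section commits to analysis as randomised. An SAP could follow the protocol faithfully and still break the randomised comparison.

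The size is conditional. Under the assumed one-sided selection, type I error is about 11% with 5 infants dropped per arm and about 7% with 3; with exclusions unrelated to arm and outcome it is 5%.

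Two further readings should be resisted. The planned sample size is not wrong, since 40 per group reproduces at 79% power. Nor do the documents support a power shortfall: falling to 38 or 34 per arm (about 77% or 72%) would mean losing 14 or 22 of 90 infants, more than the protocol's allowance of 10.

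**What to change.** Replace the exception in 11.2, and align 5.1 and 10.1 with it:

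1. The primary analysis includes all randomised infants with any ROP examination, in the arm assigned.
2. Protocol violation or stopping the study lipid is not a reason for exclusion from analysis.
3. ROP grades from routine screening after discontinuation are used unless consent for use of data is withdrawn.
4. Non-evaluable means only that no ROP examination exists, determined by someone blind to arm.
5. Any per-protocol set is supportive.
6. Infants without a ROP outcome, including deaths, are reported by arm.

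The cost is wording, because routine screening already produces the grades. Keeping non-adherent infants may dilute the effect slightly. Against that, retaining all 90 gives about 84% power instead of 79% with 80, provided all have an outcome and the assumed effect is undiluted.
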